#### Recruitment

The home care organizations will inform clients with suspected dementia and their informal caregivers about the study, and will ask if the researcher may reach out to them. When permission is given, the client and their informal caregiver will be contacted by phone, after which an information letter will be sent. After a follow-up conversation by phone, a home visit will be planned to obtain written consent. At all times, participants will be able to withdraw or decline their participation.

### Health care professionals

In this study, the physicians, general practice nurses, dentists, dental hygienists, case managers, district nurses, and home care workers will be referred to as health care professionals. In order to be eligible to participate in this study, a health care professional, practice, or organization must also meet several inclusion and exclusion criteria. The inclusion criteria are: willing to include oral health care in the practice organization; the health care professional in the general health practice is willing to use validated frailty questionnaires [25–27]; the dentist has affinity with older people; the dental practice is accessible for older and/or disabled people [28]; and the health care professional of the home care organization is willing to make an inventory of the oral health care needs of their clients. The exclusion criteria are: temporary position of a health care professional; and providing only care to a population younger than 65 years.

#### Recruitment

All health care professionals are recruited by the project team of the implementation project ‘Don’t forget the mouth!’. Before the study starts, the health care professionals will be informed through an information letter, and written consent will be obtained. At all times, health care professionals will be able to withdraw or decline their participation in this study.

### Intervention

The implementation project ‘Don’t forget the mouth!’ *(*i.e.*, the intervention)* aims to maintain and improve the oral health and the general health of community dwelling frail older people, with education and interdisciplinary collaborations. The collaborations of the health care professionals will be focused on of early recognition of decrease of daily oral hygiene care, oral health problems, and referral to colleagues if needed. Over the course of 12 months, health care professionals will attend four different meetings: two regional, and two national. The regional meetings will focus on the regional organisation of oral health care by interdisciplinary collaboration, the attitude towards oral health care, and oral health. The national meetings will focus on education about providing daily oral hygiene care, oral hygiene care for non-cooperative patients or clients, oral health, and professional oral health care.

Educational materials about daily oral hygiene care, oral health and professional oral health care have been developed for the participating health care professionals, informal caregivers, and all community dwelling frail older people, and will be available online (www.demondnietvergeten.nl). The intervention will also provide a screening-referral tool, which will be used by all health care professionals.

## Outcome variables

### Primary outcome variables

#### Oral hygiene

The primary outcome variable, oral hygiene, will be determined by oral plaque assessments. The dental plaque (DP), which is the biofilm of oral plaque present on a participant’s natural dentition, fixed dental prosthetics, and/or dental implants, will be measured according to the Silness and Löe index [29]. The dental prosthesis plaque (DPP), which is the biofilm of oral plaque present on a participant’s removable dental prostheses (RDP), will be assessed according to the Augsburger and Elahi index [30]. Both oral plaque measuring methods will be applied simultaneously if a participant has a partial dentition and one or two RDP(s).

##### Dental plaque

The DP will be classified according to the Silness and Löe index (score range.

0–3, 0 = no plaque, 1 = plaque with probing, 2 = visible plaque without probing, and 3 = abundance of plaque more than one third of the buccal side) [29], on pre-specified teeth: two molars, two premolars, and two incisors, one in the maxilla and one in the mandible (i.e.*, the 16, 21, 24, 34, 41, and 46).* If one of the pre-specified teeth is missing, the tooth distal of the absent one will be assessed. If the distal element is also absent, the next present tooth mesial of the absent one in the same quadrant will be assessed. Deviations will be noted. The DP will be assessed using a dental mirror (mirror holder: Carl Martin, 485CH chroom, Solingen, Germany; mirror: Intertek, front rhodium nr. 3, New York, United States) and a dental probe (Intertek, CP12, New York, United States).

##### Dental prosthesis plaque

The DPP will be classified according to the Augsburger and Elahi index [30]. In this method, the maxillary RDP will be rinsed, coloured with a disclosing solution, a score will be given to each of the eight planes (score range 0–4, 0 = 0% plaque, 1 = 1–25% plaque, 2 = 26–50% plaque, 3 = 51–75% plaque, and 4 = 76–100% plaque, visible) [30], and a total score will be calculated. As disclosing solution, 0.05% methylene blue (produced by pharmacy ‘De Tolgaarde’, Leusden, Netherlands) will be used. In the current study, the assessment of the mandibular RDP has been added. The DPP score will be averaged in case there are two RDPs (an maxillary and a mandibular). To facilitate reproducibility, the RDP will be placed on a specially designed reference sheet with a grid outline indicating the planes. The RDP is then photographed with a dental camera (Shofu, Eye special II, Ratingen, Germany). A pilot study showed excellent inter-rater, and intra-rater agreement for both the maxillary and mandibular RDP assessments with the described method, when performed by trained and calibrated researchers (data not yet published).

### Secondary outcome variables

Secondary outcome variables are ‘oral health’, ‘oral health related quality of life’, ‘oral health care behaviour’, ‘general health and care dependency’, and ‘compliance of the health care professionals’.

#### Oral health

The oral health will be measured with the Oral Health Assessment Tool (OHAT) for dental screening [31], a validated screening tool for non-dental health professionals which assesses eight categories with regards to oral health: lips, tongue, gums and tissues, saliva, natural teeth, dentures, oral cleanliness, and dental pain. Each category is scored in a range from 0 to 2 (0 = a healthy situation, 1 = changes in the situation, and 2 = an unhealthy situation). All scores are summed; the final score is between 0 and 16, with a lower score indicating a healthier situation.

The OHAT by Chalmers (2005) was translated into Dutch using the forward-backward approach, in compliance with the ‘Guidelines for establishing cultural equivalency of instruments’ [32]. The translation from English to Dutch was done independently by two Dutch people who are fluent in both English and Dutch ([name] and RW; a dentist and a neurobiologist, respectively). Together with a third bilingual Dutch-native speaking person (FL, dentist and orofacial pain expert), consensus was reached. This version was back-translated into English by an external professional translator. The retranslated English version was compared to the original version, and the full team ([name], RW, FL, and the professional translator) continued discussing discrepancies between the translations until consensus was reached on the final Dutch version (OHAT-NL, see Additional file 1: Appendix I).

#### Oral health related quality of life

The oral health related quality of life (OHRQoL) [33] will be measured with the Dutch version of the Geriatric Oral Health Assessment Index (GOHAI-NL) [34], a questionnaire which addresses three aspects of OHRQoL: physical function, psychosocial function, and pain/discomfort, with twelve items [34]. The simple count score (GOHAI-SC) [34, 35] will be used to dichotomize the answers for the participants. If needed, additional information from informal caregivers can be taken into account. The score options for the items are dichotomized as follows: 0 = never, seldom; 1 = sometimes, often, nearly always or always. The total score of the GOHAI-SC thus varies from 0 to 12. A higher score indicates a better experienced OHRQoL [34].

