### Statistical analysis

The personal data will be handled according the Dutch Personal Data Protection Act [40]. The data of each participant will be coded. The codes will be safeguarded by the coordinating investigator ([name]) and the principal investigator (FL). Data will be safely stored in the data management programme Castor EDC [41], and will be kept for 15 years [40]. Only the principal investigator (FL) and coordinating investigator ([name]) can fully access the final trial dataset.

Baseline comparisons between the intervention group and control group will be made using the Mann-Whitney U test. Oral hygiene will be compared at baseline, after 3, 6, and 12 months follow-up for the effect of time using the Friedman test, and the effect of group over time (intervention versus control) with the Kruskal Wallis test. The oral health and OHRQoL will also be analysed with the Mann-Whitney U test and the Kruskal Wallis test. Oral health care and the compliance of the health care professionals will be analysed according the constant comparative method of qualitative analysis [42, 43]. General health care and care dependency, will be assessed with descriptive statistics. The analysis will be conducted with IBM SPSS Statistics version 25, the level of significance will be 0.05. Protocol non-adherence is not applicable in this design. In case of missing data, imputation techniques will not be applied.

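### The printed GOHAI-SC coding and its stated direction contradict each other for any problem-worded item, so the direction of the quality-of-life score is not safely fixed

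*Protocol article*

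**What the plan says.** The protocol article defines this secondary outcome in one paragraph, under Oral health related quality of life. The instrument covers "physical function, psychosocial function, and pain/discomfort, with twelve items". Scoring is by simple count: "The simple count score (GOHAI-SC) [34, 35] will be used to dichotomize the answers for the participants". The codes are attached to the verbal answers, with one rule for the items and no exception: "0 = never, seldom; 1 = sometimes, often, nearly always or always". The range follows: "The total score of the GOHAI-SC thus varies from 0 to 12". The direction is then given: "A higher score indicates a better experienced OHRQoL".

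The Statistical analysis section does not restate a direction. It says only "The oral health and OHRQoL will also be analysed with the Mann-Whitney U test and the Kruskal Wallis test". The Discussion comments on the validity of the questionnaire in people with dementia, not on its scoring.

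The neighbouring scored outcome, the OHAT, gives 0 to a healthy category and 2 to an unhealthy one, and concludes "the final score is between 0 and 16, with a lower score indicating a healthier situation". Its coding and direction agree.

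**The concern.** The rule gives a point when the thing asked about happens sometimes or more often, and none when it happens seldom or never. If the item asks about a problem, the point marks the problem, and adding points counts problems. A count of problems rises as quality of life falls, yet the paragraph says that a rising total is good.

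At stake is the reading of a named secondary outcome. Someone who scores by the printed rule and interprets by the printed direction could report a benefit of the intervention as harm, or harm as benefit. Nothing elsewhere in the article would catch the slip. The two scored secondary outcomes also carry opposite stated directions, which makes a sign error in scoring syntax or tables easier to make and harder to notice.

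**Working it through.** **Inputs (protocol article, Oral health related quality of life)**
- Items: 12.
- Code per item: 0 for the two least frequent answers, 1 for the others.
- Reversal of items: none stated.
- Stated direction: higher is better.
- Assumption: *k*, the number of items worded so that a frequent answer is favourable. The items are not printed, so the whole range from 0 to 12 is covered.

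**Step 1: reproduce the stated range.** Minimum 12 × 0 = 0; maximum 12 × 1 = 12. The range of 0 to 12 is correct.

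**Step 2: a single item.** For an item asking how often pain occurs, always scores 1 and never scores 0. More pain raises the total. This contradicts the stated direction, whatever the other items look like.

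**Step 3: the total.** Under the one unreversed rule:
- best state (no problems, every favourable thing present): score = *k*
- worst state (every problem present, nothing favourable): score = 12 − *k*

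| *k* | Best state | Worst state | Direction at the extremes |
|---|---|---|---|
| 0 | 0 | 12 | higher = worse |
| 3 | 3 | 9 | higher = worse |
| 5 | 5 | 7 | higher = worse |
| 6 | 6 | 6 | none |
| 7 | 7 | 5 | higher = better |
| 12 | 12 | 0 | higher = better |

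The total runs against its label for *k* = 0 to 5 and has no direction at *k* = 6. From *k* = 7 to 11 it points the stated way at the extremes, but the remaining 12 − *k* items still count the wrong way. Only *k* = 12 makes the stated direction right for every item. That would require even the pain/discomfort items to ask how often the participant is free of it.

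**Step 4: effect on the planned tests.**
- *Pure reversal (k = 0).* The correctly directed score is 12 − *T*. The Mann-Whitney statistic becomes *n*₁*n*₂ − *U*. In Kruskal-Wallis each rank *R* becomes *N* + 1 − *R*, so squared deviations from the mean rank do not change. Two-sided p-values stay the same; only the group read as better is swapped.
- *Mixed wording (0 < k < 12).* Let *p* be the problems present and *f* the favourable things present. The printed rule gives *p* + *f*; a consistent problem count gives *p* + (*k* − *f*). Illustration with *k* = 3: participant A has *p* = 0 and *f* = 3; participant B has *p* = 3 and *f* = 0. The printed rule gives 0 + 3 = 3 and 3 + 0 = 3, a tie. The consistent count gives 0 + 0 = 0 and 3 + 3 = 6. The ordering itself changes, so ranks and p-values can change too.

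**The case against.** The strongest objection is that the direction depends on wording that the article does not print. Function and comfort can be asked about either way, and the scoring is cited to sources not at hand. A reader might infer that the quality-of-life result would certainly come out backwards, or that a participant free of problems certainly scores 0. The document does not support either. The second holds only if all twelve items are problem-worded, and reversal at the extremes needs fewer than six favourable items. Both also assume that the analysts apply the printed sentence literally to raw answers and do not follow the cited scoring. This part of the objection stands.

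It can also be said that an article condenses the full protocol, and that item reversal belongs to the scoring instructions or the analysis plan. That is fair as far as an unstated reversal goes; the omission alone would be no finding. But the article does more than omit. It prints a rule tied to the verbal answers and a direction, and for problem-worded items the two disagree. A citation does not show which of the two sentences is the wrong one.

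Finally, rank-test p-values survive a pure reversal. This is correct and limits the damage, but the conclusion about which group did better does not survive it, and under mixed wording the p-values are not protected either.

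**Conclusion.** The point holds in a conditional form. For every problem-worded item the printed coding contradicts the printed direction, and nothing else in the article resolves this. That pain/discomfort items are problem-worded is an expectation drawn from the name of the aspect, not a documented fact, so confidence is moderate.

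The size runs from a complete reversal of interpretation with unchanged p-values (all items problem-worded), through a total that adds opposite directions and disturbs the ranks (mixed wording), to no effect at all (all twelve favourably worded, or the scoring actually used already consistent). The first two could lead to a wrong statement about one of the five named secondary outcomes. The primary plaque outcome and the sample size are not affected. It should be corrected, but it does not threaten the main conclusion of the study.

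**What to change.** Before analysis, check the direction of each of the twelve items and state one consistent rule. Either of these works:

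1. Keep 1 for a problem present (sometimes or more often), reverse any favourably worded item before summing, and state that a higher total means worse OHRQoL.
2. Score 1 for a problem absent on every item, with favourably worded items coded to match, and keep the statement that higher is better.

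Name the reversed items, or state that there are none. The range stays 0 to 12 in both cases. A useful check in the scoring syntax is to run a constructed record with no problems and one with every problem, and confirm that they land at the intended ends of the scale.

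The cost is one sentence in the outcome definition and a few lines of syntax. Provided that the item answers are stored before dichotomising, no data collection changes.

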#### Oral health care behaviour

Information about the oral health care behaviour of the participants will be collected through two questionnaires designed for this study. The first questionnaire contains twelve items for the participant about daily oral hygiene care, difficulties with oral hygiene care, and visits to an oral health care professional. The second questionnaire contains fourteen items for the informal caregiver about their role, knowledge, and difficulties with oral health care of the participant.

#### General health and care dependency

General health and care dependency will be measured with The Older People and Informal Caregiver Survey Minimum Data Set (TOPICS-MDS) questionnaires [36], at baseline and after 12 months. These questionnaires are part of a larger national initiative to assess the Dutch senior population [36]. There are two questionnaires, one for the older person and one for the informal care giver. The questionnaire at baseline for the participant contains 51 items, the follow-up questionnaire contains 46 items; both are about demographics, morbidity, quality of life, functional limitations, emotional wellbeing, social functioning, and health service utilization [37]. The questionnaire at baseline for the informal care giver contains 27 items, the follow-up questionnaire contains 26 items; both are about demographics, hours of informal care, and quality of life [37].

Only the data collected with items about demographics, morbidity, health service utilization, and hours of informal care will be analysed in the current study to describe the population and compare the general health and care dependency between the intervention group and the control group.

#### Compliance of the health care professionals

To explore how the intervention is carried out, the compliance of the health care professionals will be assessed with questionnaires specifically designed for this study. There are six different questionnaires, three versions at baseline and three versions for the follow-up phase. There is one version for the health care professionals at the general practice, one version for the health care professionals at the dental practice, and one version for health care professionals of the home care organization. The questionnaires at baseline contain nine (home care organization) or ten (general practice and dental practice) items, about their care population, collaborations with other health care professionals, oral health care education, and oral health care organization in the practice or organization for frail older people.

The follow-up questionnaires contain eight (general practice) or nine (dental practice and home care organization) items, about the same subjects as mentioned at baseline; the item describing their care population will be left out.

### Sample size

The primary outcome variable is oral hygiene, determined by the proxy oral plaque, that will be classified according to the Silness and Loë index for dental plaque (DP) [29] and/or the Augsburger and Elahi index for dental prosthetic plaque (DPP) [30].

To calculate the sample size, a power of 80% was chosen (β = 0.20), with a significance level (α) of 0.05, expected standard deviation (σ) DP = 0.75 and DPP = 0.88 [3, 38]. For the intervention group, expected average scores were (μ^2^) DP = 1.63 and DPP = 1.60, for the control group the expected average scores were (μ^1^) DP = 2.17 and DPP = 2.13 [3, 38]. A clinically relevant effect of the intervention was set at an improvement of the oral hygiene with a DP and DPP reduction of 25% [3]. The sample size (*n*) was then calculated with the formula below [3].$$ n=\frac{2\upsigma 2}{\left({\upmu}^1-{\upmu}^2\right)2}\ f\ \left(\alpha, \beta \right) $$

To take non-parametric testing, drop-outs and loss to follow up in account, the sample size will be increased with 10% [9]. As a result, a sample size of *n* = 34 for DP and *n* = 49 for DPP would suffice.

This study will have intervention groups and control groups, and will take place in multiple towns and therefore is considered a multicentre study. With that in mind the sample size formula should be adjusted to the design effect (i.e.*,* the different towns that are participating).$$ Towns\ needed=\frac{2n\left(1+\left(m-1\right) ICC\right)}{m} $$

The expected intra class correlation is 0.03 [3, 38]. Based on a previous study [39], and the pilot study of ‘Don’t forget the mouth!’ (data not published), the expected number of participants (*m)* in each town is 20 in total, 8 for DP, and 12 for DPP. In total, at least 11 towns are needed in this study.

### Statistical analysis

The personal data will be handled according the Dutch Personal Data Protection Act [40]. The data of each participant will be coded. The codes will be safeguarded by the coordinating investigator ([name]) and the principal investigator (FL). Data will be safely stored in the data management programme Castor EDC [41], and will be kept for 15 years [40]. Only the principal investigator (FL) and coordinating investigator ([name]) can fully access the final trial dataset.

Baseline comparisons between the intervention group and control group will be made using the Mann-Whitney U test. Oral hygiene will be compared at baseline, after 3, 6, and 12 months follow-up for the effect of time using the Friedman test, and the effect of group over time (intervention versus control) with the Kruskal Wallis test. The oral health and OHRQoL will also be analysed with the Mann-Whitney U test and the Kruskal Wallis test. Oral health care and the compliance of the health care professionals will be analysed according the constant comparative method of qualitative analysis [42, 43]. General health care and care dependency, will be assessed with descriptive statistics. The analysis will be conducted with IBM SPSS Statistics version 25, the level of significance will be 0.05. Protocol non-adherence is not applicable in this design. In case of missing data, imputation techniques will not be applied.

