## Methods and design

### Study design

This protocol describes a prospective longitudinal single-blind multicentre study, which will take place in 14 towns in the Netherlands. Recruitment will take place in two districts within a town, i.e.*, an intervention group* and *a control group*, that are matched based on social-economic status and population composition, and are enrolled through the town’s home care organization. Assignment of a district to the intervention or the control group will be done ‘a priori’. The intervention group will receive care of the healthcare professionals who participate in the implementation project ‘Don’t forget the mouth!’. The control group will receive care as usual. The participants will be visited at their home for assessment, at baseline, after 3, 6, and 12 months. The health care professionals of the intervention group will receive questionnaires. All data collection will be done by the same blinded researcher, viz., a dentist trained in the geriatric dentistry. Participants will be blinded. Health care professionals participate in the intervention, and therefore they cannot be blinded. The blinding code can be broken by the supporting investigator (RW) or principal investigator (FL) in case of a medical emergency of a participant. The Data Safety Monitoring Board (DSMB) is not needed because the risk for adverse side effects in this study is determined to be negligible. An independent monitor will monitor the study data according to ‘Good Clinical Practice’(GCP).

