## Discussion

This protocol describes a prospective longitudinal single-blind multicentre study, which aims to assess the effectiveness of the implementation project ‘Don’t forget the mouth!’ focused on community dwelling older people with dementia.

As any study, this protocol has some specific strengths, weaknesses, threats, and opportunities, which will be lined out below.

The strengths of the current study are the national roll-out of the intervention, interdisciplinary collaborations and education of different health care professionals focused on knowledge, attitude and skills of oral health care, and the scientific evaluation over the course of 12 months. According to the sample size calculation 11 towns are needed for this study, while the implementation project ‘Don’t forget the mouth!’ will take place in 14 towns, providing margin for withdraws.

The possible weaknesses of assessing the effectiveness of the implementation project are selection bias from allocation, due to recruitment through the home care organization. Randomization of the districts was not possible in the described study. Participants will not explicitly be made aware of their allocation, but some will be aware of the intervention as they are receiving educational materials through their health care professionals. Another possible weakness is the fact that the GOHAI-NL is not validated for people with dementia [34]. At the time of writing the protocol, there were no validated questionnaires available to assess OHRQoL for people with dementia. The reliability of the answers of the GOHAI-NL will be increased through taking, if needed, additional information from informal caregivers to account [34]. The two questionnaires about oral health care behaviour and compliance of the health care professionals are designed for this study, and not validated, which is a weakness of these instruments.

Within the current study, there is an opportunity to additionally assess the process of the implementation. If process evaluation can be conducted, recommendations about success factors or thresholds with implementation can be made to health care professionals.

The threats are found in the recruitment procedure (through the home care organisation), different informal caregivers with each assessment, and the adherence and compliance of the health care professionals to the intervention.

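### Arms are not randomised, and the stated primary comparison takes no covariate and does not say how baseline plaque enters it

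*Protocol article*

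**What the plan says.** **Allocation.** Each town contributes two districts, one per arm. The Study design section says: "Assignment of a district to the intervention or the control group will be done" in advance. The Discussion adds: "Randomization of the districts was not possible in the described study". The two districts are chosen as pairs "that are matched based on social-economic status and population composition".

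**Recruitment.** Participants come in through the home care organisations, which first seek permission for contact: "The home care organizations will inform clients with suspected dementia and their informal caregivers about the study, and will ask if the researcher may reach" (sentence cut short here). On blinding of professionals, Study design says: "Health care professionals participate in the intervention, and therefore they cannot be blinded". Eligibility criteria for practices and professionals include willingness and interest, for example that "the dentist has affinity with older people". One exclusion, registration at a practice of the intervention group, applies to control participants only.

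**Acknowledged weakness.** The Discussion lists "selection bias from allocation, due to recruitment through the home care organization".

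**Analysis.** The Statistical analysis section says: "Baseline comparisons between the intervention group and control group will be made using the Mann-Whitney U test". It then gives a Friedman test for time and a Kruskal-Wallis test for the effect of group over time. General health and care dependency are only described, and missing data are not imputed.

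**The concern.** In a non-randomised comparison the arms may differ in plaque, cognition, dependency or attitude to mouth care before the intervention starts. The protocol recognises this, and it collects baseline plaque, MMSE, age and TOPICS-MDS data that could reduce the bias. Yet it commits the primary group comparison to a test that cannot use them.

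The baseline Mann-Whitney test does not fill the gap. A non-significant result does not show balance, and the protocol attaches no action to a significant one.

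At stake is the primary effectiveness conclusion. If one arm starts with cleaner mouths, some or all of a follow-up difference could be pre-existing, and the stated analysis could not separate the two.

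**Working it through.** **1. The plan's own figures (Sample size section).** Inputs: SD 0.75 (DP) and 0.88 (DPP); expected means 2.17 v 1.63 and 2.13 v 1.60, so differences of 0.54 and 0.53; alpha 0.05, power 80%. With two-sided alpha, f = (1.960 + 0.842)² = 7.849.

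- DP: 2 × 0.75² / 0.54² × 7.849 = 30.28; divided by 0.9 = 33.65, rounded up to 34.
- DPP: 2 × 0.88² / 0.53² × 7.849 = 43.28; divided by 0.9 = 48.08, rounded up to 49.
- Towns, DP: 2 × 34 × (1 + 7 × 0.03) / 8 = 10.29, so 11.
- Towns, DPP: 2 × 49 × (1 + 11 × 0.03) / 12 = 10.86, so 11.

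These agree with the protocol, so the sample size is not in dispute. The planned numbers per arm, assuming an equal split, are 11 × 8 / 2 = 44 (DP) and 11 × 12 / 2 = 66 (DPP). With 14 towns they are 56 and 84. The 34 and 49 are values before the design effect and are not used below.

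**2. Assumptions.** The documents give no size for a baseline imbalance and no baseline/follow-up correlation. I assume a difference d = 0.25 SD (0.19 DP points, 0.22 DPP points) and a correlation rho of 0.5 to 0.7. There is no true effect, and clustering is ignored. A normal approximation stands in for the rank test.

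Rejection probability: P = Φ(x − 1.96) + Φ(−x − 1.96).

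**3. Test on raw follow-up scores.**

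*Stable difference*, x = d × √(n/2):

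| | n per arm | x | P |
|---|---|---|---|
| DP, 11 towns | 44 | 1.173 | 22% |
| DPP, 11 towns | 66 | 1.436 | 30% |
| DP, 14 towns | 56 | 1.323 | 26% |
| DPP, 14 towns | 84 | 1.620 | 37% |

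The spurious difference is 0.1875/0.54 = 35% of the DP target and 0.22/0.53 = 42% of the DPP target.

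*Only the correlated part carries forward*, x = d × rho × √(n/2), at 11 towns:

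- DP: 9% (rho 0.5) to 13% (rho 0.7).
- DPP: 11% to 17%.

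**4. Test on change scores.** A stable difference cancels and the error rate stays near 5%. If instead the imbalance partly regresses, change scores overshoot by d × (1 − rho) SD against the arm with the better baseline. For DP at d = 0.25 this is 0.25 × 0.3 × 0.75 = 0.06 to 0.25 × 0.5 × 0.75 = 0.09 points. Other measured confounders stay unadjusted.

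**5. The baseline test as a safeguard.** Its power against a 0.25 SD difference follows the formula in step 3: about 22% (DP) and 30% (DPP) at 11 towns. It misses such a difference in most trials. At 0.5 SD its power is about 65% and 82%.

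**6. Does baseline adjustment alone solve it?** If the imbalance regresses, yes: simulated rejection for DP stays at about 5% to 6%. If the difference is stable, adjustment leaves d × (1 − rho). With residual SD √(1 − rho²), x = d × √((1 − rho)/(1 + rho)) × √(n/2). At 44 to 66 per arm, P is about 8% to 13% for d = 0.25 and about 17% to 38% for d = 0.5. Baseline adjustment and change from baseline each fail where the other works.

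**The case against.** **The protocol does respond to imbalance in its design.** It pairs districts within a town on two factors, restricts MMSE to a narrow band, and uses one blinded assessor. A reader might infer that the baseline test is the only response; the documents do not support that. But the matching factors are area-level, do not balance individual plaque, dependency or practice motivation, and the pairs are ignored in the analysis. Blinded assessment protects measurement, not selection.

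**The Kruskal-Wallis test may be meant for change scores.** The wording about group over time allows this, and a stable baseline difference would then do no harm. It would be wrong to state as fact that baseline plaque is ignored. What stands is that the text does not say which, and neither reading handles other confounders.

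**No imbalance is documented.** A reader might infer that baseline differences will be reported as an intervention effect. The documents do not support that: the size is unknown, baseline comparisons are planned, and the bias is disclosed. That recruiters know the allocation is also an inference, though a direct one from the unblinded professionals and the advance assignment. Disclosure, however, does not correct the estimate.

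**Covariates may be left to an analysis plan.** A list may be. But the protocol names the primary test, and that test cannot take one.

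**Conclusion.** The concern holds in a limited form. For a non-randomised design with acknowledged selection bias, the protocol fixes a primary comparison that takes no covariate, pair or town, and leaves open how baseline plaque enters it.

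Under the raw-score reading, an assumed 0.25 SD imbalance raises the false-positive rate of a single follow-up test from 5% to about 22–30% if stable, or about 9–17% if only the correlated part persists (11 towns, no clustering). Under the change-score reading, a stable imbalance has no such effect, but regression to the mean and other confounders remain. The imbalance and the correlation are assumptions. They show sensitivity and do not predict what this trial will find.

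A reader might also infer that adjusting for baseline plaque alone cures the problem. Step 6 of the working shows that it does not if the difference is stable.

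**What to change.** In the Statistical analysis section:

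- Replace the Kruskal-Wallis comparison as primary analysis with a pre-specified longitudinal model of DP, and separately of DPP, at 3, 6 and 12 months. Adjust for the participant's own baseline plaque and a short list of baseline covariates, with town (the district pair) as a random effect. Age, MMSE, prosthesis status, and either hours of informal care or morbidity would serve. The last two are among the TOPICS-MDS items that the General health and care dependency section already sets aside for analysis. Keep the list short: 11 towns give about 88 DP participants.
- Report change from baseline (difference-in-differences) alongside it, and require the conclusion to hold under both.
- Describe baseline imbalance with standardised differences and drop the significance test.

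Cost: no new data collection, but not free. A model assumption replaces a rank test, and without imputation participants with missing covariates are lost. Adjustment covers measured confounders only, so the limitation stated in the Discussion should stay.
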